### Missing data

Based on prior studies conducted in the Wills Eye Glaucoma Research Center, we anticipated losing approximately 5 % of enrolled patients per year (total 20 % across 4 years) due to attrition. Both mixed effects models and the GCMMs include all available data from all patients under the assumption that any missing data are missing at random. This is the approach researchers will take for the study’s primary analysis. As a sensitivity analysis, researchers will fit the final models using only patients with data from all visits.

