### Statistical analysis and sample size justification

*Primary Outcome Variables* will be divided into three groups: 1) QoL (NEI-VFQ-25 and MGSS) 2) performance-based measures of visual function (CAARV) and 3) Clinical measures of vision (better and worse eye VF mean defect, better and worse eye VA, and binocular SPARCS contrast sensitivity). *Primary Exposure/Demographic Variables* will be characterized as baseline DDLS score, age, ethnicity, gender, type of glaucoma, and number of medical comorbidities. *Secondary Variables* will be characterized as better and worse eye IOP, treatments, and duration of treatment.

All primary and secondary variables measured at baseline will be compared using means, medians, standard deviations, ranges or frequencies, and percentages. At baseline, Spearman correlation coefficients will be provided for all pairs of outcome variables and demographic variables.

In order to characterize the longitudinal trajectory of VRQoL, clinical measures of vision, and vision-related functioning over a 4-year period, analysis of these outcomes will proceed in two stages. First, mixed effects linear regression will be used to model the average trajectory of the sample. This will identify the appropriate parametric forms for each outcome trajectory. The study collects outcomes at five different timepoints over the 4-year study period. Linear and quadratic curves will be calculated, as well as a saturated model that treats time as a categorical explanatory variable. This allows for estimation of the mean outcome score for each visit. The mixed effects model will account for correlation among repeated measurements from the same patient. Our goal in these analyses is to identify the most parsimonious model that adequately represents the shape of the outcome trajectory over time. Ideally, a linear model will be sufficient. It is possible, however, to imagine scenarios where a quadratic term may be required (e.g., initial decline followed by stabilization).

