No sample size formulae exist for GCMM. A sufficient sample size of 160 patients was chosen in order to identify subgroups using the latent class analysis. The primary goal of this analysis is to estimate parameters of the trajectory in each class with appropriate precision. The precision of the confidence interval will be calculated for the class- and outcome-specific slopes, assuming that a linear model is sufficient to describe the trajectory of a particular outcome. Class sizes will vary based on outcome. For illustration, we estimated precision for class sizes of 20, 60, and 100. Each patient will have up to five observations. Assuming 5 % dropout per year, the average number of observations per patient is 4.5.

Table 5 shows the width of the confidence interval for the slopes for NEI-VFQ-25 Total Score and LogMAR VA. For reference, a slope of one would indicate a 12-unit change in the NEI-VFQ over 12 months. A slope of 0.01 for LogMAR would indicate a change of 0.12 units over 12 months. The calculations given in Table 5 assume an intra-subject correlation of 0.2. Higher values within subject correlation would result in less precision while lower correlation would result in increased precision.

**Table 5 Tab5:** Sample confidence intervals for slopes of NEI-VFQ-25 and visual acuity

Number of subjects per class	Effective Sample Size N*4.5/(1 + (4.5-1)*0.2)	Distance from slope estimate to the two-sided 95 % confidence limits for the class-specific slope	
		NEI-VFQ (Std. Dev = 17)	LogMAR VA (Std. Dev = 0.2)
20	53	+/− 0.28	+/− 0.0033
60	159	+/− 0.16	+/− 0.0019
100	265	+/− 0.12	+/− 0.0014

*NEI-VFQ-25* National eye instate vision function questionnaire; LogMAR VA

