## Discussion

“How can I improve, or at least maintain, the overall health and well being of my patients?” – is one of the most important questions every ophthalmologist should ask himself or herself, especially when treating patients with glaucoma.

Many visually impaired individuals have difficulty performing daily activities, such as reading, writing, eating, dressing and traveling from place to place. These difficulties tend to be even more pronounced in elderly patients, who may also have cognitive decline or other physical ailments in addition to their visual impairment. Understanding the impact of these difficulties on an individual’s QoL and how they are able to function in their daily lives is important and may have direct implication on clinical decision-making.

VRQoL is an elusive term, the meaning of which is it may vary widely between clinicians and their patients. Two patients with the same degree of visual impairment may have very different views on their VRQoL. In order to understand the impact of visual impairment on the ability of individuals to function, performance-based measures have been developed [16–18, 33–39]. The advantage of performance-based measures is that they provide an objective measurement of a patient’s abilities using standardized criteria. Ophthalmologists rarely assess patients’ performance-based functional ability, assuming that surrogates such as subjective self-report on well-being, VF, and VA are appropriate proxies [19, 40]. However, these proxies do not necessarily correlate with performance-based measures; further, some may be more important or relevant than others. Richman et al. investigated the relationships among three methods of assessing visual loss caused by glaucoma: (1) standard clinical tests of vision, (2) self-reported QoL, and (3) the ability to perform activities of daily living, which was assessed by ADREV. They concluded that performance-based testing and QoL evaluations were both independently important measures of health, and although related, were by no means the same [18].

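### The stage-1 mixed models rest missing at random on time and each outcome's own history alone, so collected predictors of dropout go unused; any bias is modest and its direction depends on who leaves

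*Protocol article*

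**What the plan says.** Under Missing data, the protocol article expects "losing approximately 5 % of enrolled patients per year (total 20 % across 4 years) due to attrition". It then states that mixed models and GCMMs alike "include all available data from all patients under the assumption that any missing data are missing at random", and adds: "This is the approach researchers will take for the study’s primary analysis". The one sensitivity analysis is that "researchers will fit the final models using only patients with data from all visits".

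The models are described under Statistical analysis and sample size justification. In stage 1, "mixed effects linear regression will be used to model the average trajectory of the sample". Time is the only explanatory variable named: "Linear and quadratic curves will be calculated, as well as a saturated model that treats time as a categorical explanatory variable". Correlation among a patient's repeated measurements is also modelled.

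In stage 2, baseline exposure and demographic variables enter the GCMM through the class-probability part. The same section defines these to include DDLS score, age and number of medical comorbidities. A further extension models the trajectories of the primary outcomes jointly. Stage 1 guides the choice of trajectory shape for stage 2.

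The article gives a dropout rate. It does not say who is expected to leave, or why.

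**The concern.** Missing at random is not a property of the data alone. For a likelihood analysis of one outcome, it requires that dropout, given what is in the model, carries no further information about the values not seen. With only time and the outcome's own history in the model, that condition fails when two things are both true: dropout is related to another variable, such as age or visual field, and that variable still predicts the unseen outcome once the patient's own earlier values are known.

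The study collects the obvious candidates. DDLS, age and comorbidity count are recorded at baseline, and visual field, visual acuity, contrast sensitivity and CAARV are repeated at the annual visits. In stage 1, as described, none of these supports the missing-data assumption for, say, NEI-VFQ-25. If such variables drive dropout, the patients who stay stand in for patients with a different course, and the average trajectory is shifted although the data to correct it are in hand.

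**Working it through.** **1. The article's own figures.** With 5% of enrolled patients lost per year, mean observations per patient = 1 + 0.95 + 0.90 + 0.85 + 0.80 = 4.5, as stated ("Assuming 5 % dropout per year, the average number of observations per patient is 4.5").

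Table 5: effective N = N × 4.5 / (1 + 3.5 × 0.2), which is 52.9, 158.8 and 264.7 for N = 20, 60 and 100. The half-width per month is t × SD / (SD of time × √effective N). With visits at 0, 12, 24, 36 and 48 months, the SD of time is 16.97 months. For NEI-VFQ-25 (SD 17) this gives 0.28, 0.16 and 0.12, as printed. The inputs are sound, and dropout enters them only through the number of observations.

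**2. Sampling error for the whole-sample slope.**
- Table 5 formula, 161 patients: effective N = 161 × 4.5 / 1.7 = 426.2. Half-width = 1.966 × 17 / (16.97 × √426.2) = 0.0954 per month, about 1.14 points per year, so a standard error (SE) of about 0.58.
- Random-intercept, random-slope model with independent residuals and complete data: variance = (residual variance / 10 + slope variance) / 161, where 10 is the sum of squared deviations of the visit years. With a slope SD of 1 point/year:
  - correlation 0.2: (231.2/10 + 1)/161 = 0.150, SE 0.39;
  - correlation 0.7: (86.7/10 + 1)/161 = 0.060, SE 0.25.

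The second formula is the more demanding yardstick, because it makes a given bias look larger.

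**3. Simulated bias.** Taken from the documents: NEI-VFQ-25 SD 17, five annual visits, and retention of 95, 90, 85 and 80%. Assumed: true decline of 1 or 2 points/year; slope SD 1; within-patient correlation 0.2 (the article's value) or 0.7; correlation 0.3 or 0.6 between the random effects of NEI-VFQ-25 and a clinical measure; a baseline covariate correlated −0.3 with slope; and dropout log-odds of 0.7 to 1.4 in size per unit of the driver. Each scenario had 400,000 patients, a saturated mean and an unstructured covariance. The table shows error in the 4-year change, in points, for a decline of 2 points/year and both correlations at their article or upper values (0.2 and 0.6).

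| What drives dropout | Own history only | Plus clinical measure and covariate | Completers only |
|---|---|---|---|
| Worse clinical measure, log-odds 0.7 | +0.50 | 0.00 | +0.17 |
| Worse clinical measure, log-odds 1.4 | +0.83 | 0.00 | +0.28 |
| Better clinical measure, log-odds 0.7 in size | −0.52 | −0.01 | −0.22 |
| Baseline covariate, 0.7 | +0.14 | −0.01 | +0.17 |
| Outcome's own past, 0.7 | 0.00 | 0.00 | −0.40 |

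A plus sign means that decline is understated. Over all scenarios:
- If worse patients leave, decline is understated by 0.13 to 0.85 points over 4 years (0.03 to 0.21 per year).
- If better patients leave, it is overstated by 0.15 to 0.52 points.
- If dropout follows the outcome's own past, bias is about zero.
- Conditioning on the clinical measure and covariate leaves at most 0.03 points.

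**4. Size against sampling error.** The largest slope biases are 0.205/0.39 = 0.53 SE (correlation 0.2) and 0.128/0.25 = 0.51 SE (correlation 0.7). The smallest are about 0.1 SE. Against the Table 5 SE, the largest is 0.21/0.58 = 0.36.

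**5. A second simulation with larger slope variation.** This assumed a decline of 1.5 points/year, slope SD 1.5 to 2.5, correlation 0.7, and dropout through age and visual field. The own-outcome model understated decline by 3.5 to 15% (0.2 to 0.8 SE), with 95% interval coverage between 95% and 88%. In its central case the true slope was −1.503. The estimates were −1.364 with own history only, −1.461 after adding age and age × time, and −1.502 after also adding the visual field series. Age with its time interaction thus removed 0.097 of 0.139, about 70%.

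**6. Does the planned sensitivity analysis reveal the problem?** No. Completers are off by −0.10 to −0.43 points where the primary model is unbiased. When a baseline covariate drives dropout, both analyses err by about the same amount (+0.14 and +0.17 above), so their agreement would be falsely reassuring.

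**The case against.** A reader might infer that the plan understates decline. The documents do not support that. They give no dropout mechanism, and the sign reverses or vanishes with the mechanism assumed. The Discussion remark "These difficulties tend to be even more pronounced in elderly patients" concerns daily activities, not attrition. The eligibility criteria exclude dementia, neurological or musculoskeletal disease that would affect daily activities, and patients unlikely to be available for 4 years. Recruitment excludes DDLS stages 9 and 10, and there are active retention measures. All of this works against dropout through illness or severe field loss.

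A reader might also infer that missing at random fails whenever dropout is related to age or field. That is too strong: such a variable matters only if it still predicts the unseen outcome given the observed history.

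Nor does the point extend to the whole primary analysis. The GCMM uses the baseline variables in class membership, and the joint GCMM uses the other primary outcomes. What remains is that a single-outcome GCMM does not use the other outcomes' histories, and that the joint model serves the question of concurrent change rather than the stage-1 average. The documents do not present stage 1 as the headline result either; its stated purpose is to find the trajectory shape. The simulations address bias in level and slope. They do not show that the choice among linear, quadratic and categorical time would change.

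Finally, using all available data under missing at random is a standard primary approach, and covariates may be set in an analysis plan not shown. That lowers the weight of the point. It does not remove it, because the article fixes the missing-data assumption and describes the model that carries it.

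**Conclusion.** The point holds as a conditional one about stage 1. As described, the assumption there is narrower than the collected data allow, and the average trajectory may be biased if dropout runs through age, comorbidity, disc damage or visual field beyond what the outcome's own history captures. Direction cannot be stated in advance.

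The size is modest: roughly 0.03 to 0.2 NEI-VFQ-25 points per year, mostly 0.1 to 0.5 SE, and up to 0.8 SE under the steeper assumptions. These figures rest on assumed slopes, correlations and dropout strengths that the article does not give. Nothing in the Missing data section is wrong in itself. This is a cheap improvement, not an error that endangers the study.

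**What to change.** Keep all available data. In each stage-1 mixed model add baseline age, comorbidity count and DDLS score, each with a time interaction, and report the fitted trajectory averaged over all 161 enrolled patients, so that it still describes the whole sample.

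Baseline covariates help only as far as dropout runs through them. As an optional sensitivity analysis, add one short auxiliary series, such as better-eye visual field mean defect, by multiple imputation or joint maximum likelihood. This would also examine the assumption in a way that the completers-only refit cannot.

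The cost is some programming and a few extra parameters per model; no new data are needed. A larger auxiliary set is not advisable. Four series at five visits are 20 measurements, or 20 × 21 / 2 = 210 covariance parameters if unstructured, which is too heavy for 161 patients.

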## Discussion

“How can I improve, or at least maintain, the overall health and well being of my patients?” – is one of the most important questions every ophthalmologist should ask himself or herself, especially when treating patients with glaucoma.

Many visually impaired individuals have difficulty performing daily activities, such as reading, writing, eating, dressing and traveling from place to place. These difficulties tend to be even more pronounced in elderly patients, who may also have cognitive decline or other physical ailments in addition to their visual impairment. Understanding the impact of these difficulties on an individual’s QoL and how they are able to function in their daily lives is important and may have direct implication on clinical decision-making.

VRQoL is an elusive term, the meaning of which is it may vary widely between clinicians and their patients. Two patients with the same degree of visual impairment may have very different views on their VRQoL. In order to understand the impact of visual impairment on the ability of individuals to function, performance-based measures have been developed [16–18, 33–39]. The advantage of performance-based measures is that they provide an objective measurement of a patient’s abilities using standardized criteria. Ophthalmologists rarely assess patients’ performance-based functional ability, assuming that surrogates such as subjective self-report on well-being, VF, and VA are appropriate proxies [19, 40]. However, these proxies do not necessarily correlate with performance-based measures; further, some may be more important or relevant than others. Richman et al. investigated the relationships among three methods of assessing visual loss caused by glaucoma: (1) standard clinical tests of vision, (2) self-reported QoL, and (3) the ability to perform activities of daily living, which was assessed by ADREV. They concluded that performance-based testing and QoL evaluations were both independently important measures of health, and although related, were by no means the same [18].

The current study aims to investigate the complex relationships between between clinical measures (e.g., VA, IOP, VF, OCT and CS tests), performance-based measures (assessed by the CAARV), and subjective self-reported measures (NEI-VFQ-25 and MGSS). One of the major strengths of this study is investigation of change in these relationships over a 4-year period. The patients included in this study, diagnosed with moderate-stage glaucoma, are more likely to show progression over 4 years, compared to patients with earlier stage of the disease who were excluded from this study. We also excluded patients with advanced disease, who have already shown significant disease progression.

Previous studies have highlighted the importance of binocular visual acuity and contrast sensitivity as predictors of a patient’s ability to perform activities of daily living [17].

In the current study, we used the SPARCS test to measure contrast sensitivity, in addition to the PR test. The SPARCS, a novel computerized-based CS test, is able to differentiate between patients with glaucoma in comparison to normal controls, and may have the potential of becoming a useful surrogate for performance-based measures [26].

In summary, the results of this ongoing, prospective, longitudinal, observational cohort study are expected to provide useful information on how patients with glaucoma feel and function over a 4-year period. It is likely to identify the rate of change in VRQoL and ability to function compared with disease progression over time. The results of this study may allow clinicians to understand better how clinical measures reflect objective and subjective measures of QoL in this patient population.
